## Abstract

**Background:**

The management of unruptured brain arteriovenous malformation (AVM) patients remains controversial. Furthermore, curative attempts to treat *ruptured* AVM patients have not been questioned so far, and there is a lack of prospective data on clinical results according to treatment modality. Endovascular treatment is often used aiming to improve the safety or efficacy of surgery or radiation therapy, but benefits have never been documented in a trial. A care trial context is needed to evaluate interventions at the same time they are practised.

**Methods/Trial design:**

TOBAS is a pragmatic, prospective, multicenter, randomized, controlled trial and registry which offers a care trial context for brain AVM patients, including surgical resection, radiosurgery or endovascular embolization, alone or combined. The study includes two RCTs and a multimodality prospective registry. The objectives of the proposed study are to assess whether preventive interventions (surgery, embolization, radiation therapy, alone or combined), selected by the local treatment team and performed as locally practiced, randomly allocated and compared with conservative management, in unruptured brain AVM patients eligible for active or conservative management, can improve the proportion of patients having an independent outcome (modified Rankin Scale (mRS) < 3, as assessed by a standardized questionnaire administered by non-masked care personnel) at 10 years. All patients judged ineligible for randomized allocation are to be entered in a multimodal registry. The objective of a nested trial in patients with ruptured or unruptured AVMs to be treated by surgery or radiation therapy, is to assess whether pre-surgical or pre-radiation embolization, randomly allocated and compared with no embolization, can improve the proportion of patients with complete eradication of the AVM, as locally adjudicated, combined with a good clinical outcome (mRS < 3). The study will require up to 2000 patients in approximately 30 centers or more, followed for 10 years. TOBAS is registered at clinicaltrials.gov: NCT02098252 as of 25 March 2014.

**Electronic supplementary material:**

The online version of this article (doi:10.1186/s13063-015-1019-0) contains supplementary material, which is available to authorized users.

## Background

Cerebral arteriovenous malformations (AVMs) are complex, heterogeneous, uncommon lesions that can lead to significant neurological disability or death, most commonly from intracranial hemorrhage (ICH) [1, 2]. Intracranial AVMs are typically diagnosed before the age of 40, approximately 40–50 % with a hemorrhagic presentation. An AVM-related seizure is reported as the presenting feature in 20–35 % of cases and although these can be successfully managed with anti-epileptic agents, some AVMs lead to intractable seizures in spite of medication. Other presentations include headaches or focal neurological deficits. AVMs can also be incidental findings during investigation of unrelated symptoms. Population-based data suggest that the annual incidence of discovery of a symptomatic AVM is approximately 1 per 100,000 population [1–5].

The management of brain AVMs is controversial and complex. Three different modalities are currently used (surgical resection; endovascular embolization; radiotherapy) alone or in various combinations, depending on local expertise, size, location of the lesion, and clinical presentation. Over the last decade, there has been an evolution of microsurgical as well as endovascular and radiosurgical techniques to treat these lesions [6–13]. As the management options have evolved, individual and combined modality treatment protocols have developed in various directions in different institutions. The choice of management is largely dependent on the decisions of the local physicians that make up the treatment team, and a recent survey has demonstrated substantial variability in decision-making for almost all types of AVMs [14]. Interventional therapies, when they are performed, are assumed to decrease the risk of initial or subsequent hemorrhage and, therefore, lead to better long-term outcomes, an assumption that has yet to be proven, since none of the treatment modalities or combinations thereof has been shown to improve outcomes for brain AVM patients. While microsurgical removal may provide a relatively safe and immediate cure for superficial AVMs in non-eloquent brain, resection of malformations in certain locations with a large nidus, deep draining veins, or high-flow shunts may carry a relatively high risk of morbidity [11, 13, 15–17]. Embolization can be performed with curative intent for some AVMs with favorable angio-architecture. Recently, embolization with Onyx has increasingly been proposed as a primary curative procedure [18–20]. This treatment modality is also performed as an adjunct to other modalities, either to render surgery technically simpler and possibly with less morbidity, or to reduce the AVM size to make it more conducive to cure with radiation therapy. The potential benefits of pre-surgical embolization have never been proven. Therapy may be initiated with a number of embolization sessions, typically over a span of several months. When endovascular treatment sessions have not successfully obliterated the AVM, treatment may be completed by radiation therapy, which takes 2–3 years to occlude the AVM in up to 80 % of cases if the nidus has been rendered relatively small (2 cm or less) [10]. As with embolization, radiation therapy can also be performed primarily with curative intent, particularly for small, surgically inaccessible or less safely accessible lesions. The merits of endovascular treatment prior to radiation therapy have been questioned, as the presence of endovascular material has been purported to hinder the obliteration of AVMs treated with radiation therapy, although this too remains contentious [21–23].

Irrespective of initial treatment modality chosen, therapy is sometimes suspended or interrupted because of a complication (transient or permanent). The benefits of pre-surgical or pre-radiation therapy embolization have recently been questioned [10, 24]. Although the question of which AVM treatment modality is the most appropriate first choice remains controversial, consensus can be reached in some circumstances. Surgical evacuation of a life-threatening hematoma exerting significant mass effect may remain uncontested, even though many patients with a hemorrhagic presentation do not necessarily meet this threshold for surgical intervention. Almost all other management choices remain debatable. A systematic review has proposed that approximately 7.1 % of surgical candidates, 6.6 % of endovascular candidates, and 5.1 % of radiosurgical candidates experience permanent neurological deficits after treatment, with outcomes certainly influenced by case selection [13]. The epidemiological study of Davies et al., using the Nationwide Inpatient Sample (NIS) data base and surrogates such as location at discharge, compared outcomes following AVM treatment with the different modalities, and found the worst outcomes were obtained when endovascular treatment was combined with surgical management, for both ruptured and unruptured AVMs [7]. All current therapeutic options involve substantial risks of mortality and morbidity (ranging from 1–30 %; reviewed in [10, 11, 13]) and benefits have never been shown in randomized trials. For decades the management of brain AVMs has been based on a comparison between the risks of conservative management, or the so-called natural history of the disease (the risks of rupture according to various characteristics of a particular lesion in a particular patient) and the risks of treatments judged to be most appropriate for each patient. Although this rationale makes intuitive sense, it is based on assumptions that have never been validated and on extrapolations of data from error-prone observational studies over the lifetime of patients with AVMs [25].

The natural history studies indicate an overall risk of initial hemorrhage of approximately 1–4 % per year, although the long-term consequences in terms of the probability of death or long-term disability following ICH remain unclear [26–31]. Mortality from the first hemorrhage has been reported to occur between 10–30 % of patients with a ruptured AVM, but some recent data suggest that the mortality rate may be lower, and perhaps only 10–20 % of survivors have long-term disability [27, 30]. Hemorrhagic presentation is considered the most reliable risk factor for a repeat hemorrhage [26, 27, 29]. Other risk factors, such as deep venous drainage, are less consistently identified, and typically may entail not only a higher risk of rupture without treatment, but also a higher risk of treatment. Thus, the first distinction to be made regarding AVM patients is whether or not they present with ICH. Because ruptured brain AVMs presumably have a higher hemorrhage risk (4.5–34 %) than unruptured ones (0.9 –8 %) [32], interventional treatment is perhaps advisable [2, 17, 33] at least in some patients, despite the absence of evidence from randomized controlled trials (RCTs) that the benefits outweigh the risks [6]. More controversial is the management of unruptured brain AVMs.

Recently, the results of A Randomized Trial of Unruptured Brain AVMs (ARUBA), the only RCT on AVMs, were published [34]. This ambitious trial sought to compare the outcomes of patients with unruptured AVMs following random allocation of treatment versus conservative management strategies. Patients were included only if they had no prior history or imaging evidence of a previous hemorrhage. The original study plan was to randomize 800 patients and examine the primary outcome, a composite measure of stroke and death (from any cause). The design was later revised to accommodate low recruitment rates [34]. Interventional management, when allocated, was decided locally by the care team and included endovascular, surgical, and/or radiation therapy, alone or in combination. The study was stopped by the Data Safety Monitoring Board (DSMB) after 6 years, and after enrollment of 223 patients who had been followed a mean of 33 months. The primary outcome was observed in 11 patients randomized to medical management (10 %) and 33 patients randomized to interventional therapy (29 %). Whether or not this disparity in outcome will persist as the study continues remains to be seen. The results confirm previous data with a 2.2 % (95 % CI 0 · 9–4 · 5) annualized hemorrhage risk for patients followed up without interventional therapy. Although ARUBA does offer the most reliable information on unruptured AVMs so far, the study has been criticized in many ways [35–38]: recruitment was meagre, with approximately one patient per year per center; generalizability of results has been questioned, given the small total number of patients and the small proportion of screened patients that were actually included in the study (226/1740 or 13 %) [25]. Only five patients were allocated to neurosurgery alone (12 combined with embolization), even though 76 (65 %) of the patients in the treated group were Spetzler-Martin (SM) grade I or II, which are cases typically managed with surgical resection alone, the modality considered to be the “gold standard” for these lesions in many centers, particularly in North America. For a disease with a long natural history, a mean follow-up of 33 months (SD 19 · 7) has been considered too short to support the potential benefits of curative treatments or to meaningfully compare events. The short follow-up favours the medical management group because all risk is accepted early with interventional therapy. Finally, the primary endpoint of stroke or death, with “stroke” defined as “any new focal neurologic deficit, seizure, or new onset headache associated with imaging findings of hemorrhage or infarction” may have included too many minor or transient events, considering that curative treatment aims to reduce lifetime risks of life-threatening or debilitating hemorrhages [36]. Because of the small total number of patients, heterogeneity of the population, and non-standardized management choices, the role for curative treatments of unruptured brain AVMs may remain uncertain, even once the long-term results of ARUBA become available. In the meantime, in the presence of such uncertainty, some authors have declared invasive curative treatments to be “experimental therapy” [39]. A recent observational study of Scottish cohorts followed for 12 years, reporting statistics similar to ARUBA, concluded that conservative management of unruptured AVMs was superior [40]. Although no clinical trial data exist on the effect of interventional therapy even after AVM hemorrhage, the most contentious issue at present is whether interventional therapy should be offered to patients with unruptured AVMs. In such patients, the best management strategy remains unknown, but the burden of proof is on those offering the potentially risky preventive interventions. In such a context, interventions may be best proposed in the context of a care trial [41]. TOBAS (Treatment of Brain Arteriovenous Malformations Study) is a study that addresses this crucial question of conservative versus interventional management for AVMs judged appropriate for either management paradigm.

The next important problem addressed by TOBAS is the role of adjunct embolization in patients with ruptured or unruptured AVMs treated with surgery or radiosurgery. Although endovascular AVM embolization can occasionally eradicate lesions before surgery or radiation therapy [20], and although embolization may potentially improve the safety and efficacy of surgical or radiosurgical treatments, it remains contentious whether it is worthwhile to accept the additional risks of endovascular treatment for a greater overall benefit for patients with brain AVMs that are treatable by surgery or radiation therapy alone. It is possible that the overall morbidity and mortality of the combined interventional management strategy is increased when embolization is added to a surgical or radiosurgical procedure [24, 42]. Therefore, pre-surgical or pre-radiosurgical embolization can be offered, but given such uncertainty, it may be best offered only as a randomized allocation between embolization or no embolization, within the context of a proper trial. This second randomized allocation has, therefore, been nested within TOBAS.

### Objectives

The general objective of the TOBAS trial is to offer a care trial context for the management of patients with brain AVMs (ruptured or unruptured) [41].

The primary objective of the first randomized study is to compare the effect of conservative versus interventional management (i.e. neurosurgery, radiosurgery, embolization, alone or combined) on a composite of disabling stroke or death from any cause at 10 years in patients with unruptured AVMs (patients with ruptured AVMs will be analyzed separately in secondary analyses).

The primary objective of the second randomized study is to compare the effects of embolization prior to neurosurgery or radiotherapy versus neurosurgery or radiotherapy alone, in the management of patients with ruptured or unruptured AVMs, on a composite outcome of complete obliteration of the AVM combined with an independent functional outcome at the end of the management plan.

## Methods

### Trial design

TOBAS is a prospective study that includes 2 multicenter pragmatic 2-arm parallel group RCTs using a 1:1 ratio and a clinical registry of patients managed outside the RCTs. The complete protocol is available at www.clinical-care-trials.org.

### Patients

All patients with an AVM diagnosed at a participating clinical center will be candidates for the study. Patients with unruptured AVMs considered for curative treatment, without contraindication to intervention, will be candidates for the randomized allocation of management between interventional and conservative management. All patients judged by the multidisciplinary team as potential beneficiaries from endovascular therapy as pre-surgical or pre-radiosurgical treatment will also be candidates for the nested randomized study on pre-embolization. The nested study is a randomization between embolization or no embolization for patients allocated to or being prescribed surgery or radiation therapy (when treatment is judged possible with or without embolization). Patients may be referred for enrollment by their clinical neurologist, neurosurgeon, or interventional radiologist.

### Participating centers

Participating centers are expert referral centers that can provide multidisciplinary and multimodality care for brain AVMs. There is no requirement for a minimal number of procedures (per center or per surgeon per year) but the experience of centers will be recorded.

### Eligibility criteria

TOBAS is a pragmatic care trial [41]. Any patient with a brain AVM can be included in the randomized trial or registry portion of the study.

### Study interventions

All patients participating in the trial will receive “standard medical care,” including stroke risk factor reduction (smoking, hypertension, diabetes, hyperlipidemia) as routinely, locally performed, irrespective of treatment allocation.

### Medical management

Patients allocated to the medical management arm will receive no additional interventional treatment.

### Interventional therapy

A patient allocated to interventional therapy is expected to begin interventional therapy within 3 months following randomization. Interventional therapy consists of either endovascular attempts to occlude the nidus and feeding vessels, microsurgery for resecting the AVM itself, or radiosurgery, alone or in combination, and with the various locally recommended timing of each treatment session. Interventions are applied flexibly, as in normal practice, and there is no standardization required per protocol.

Endovascular treatment may include AVM embolization, or even coiling of aneurysms in the vascular territories feeding the AVM (AVM-related aneurysm). The embolization materials used for those who undergo embolization as part of the treatment plan will be limited to those agents approved by the Food and Drug Administration (FDA) or by the approval agency applicable to the country in which the patient receives treatment at the time of the procedure. This plan allows for the introduction of new agents during the course of the study. The name of the agent and the frequency of use will be recorded on the Interventional Therapy Form.

Microsurgery may include AVM resection, and aneurysm clipping related to AVM. The operating time and the necessity of transfusions will be recorded on the Interventional Therapy Form.

Radiotherapy involves the targeting of the AVM nidus and adjacent vessels intended to induce a reduction in AVM size, and possible obliteration, of the AVM. Based on local patterns of practice, variations exist in the type of equipment used, the methods of measurement used to assess the location and size of the AVM chosen for therapy, the individual doses and numbers of treatments, and whether radiosurgery is used before or after embolization or microsurgery. The modality, energy, number of isocenters, collimator size, prescription and duration of treatment will be recorded on the Interventional Therapy Form.

The goal of the interventional therapy is to achieve eradication of the AVM. The eradication plan may include any or a combination of endovascular, surgical, or radiotherapy treatments. Following interventional therapy, using a diagnostically relevant imaging study, treatment outcome will be documented as: complete AVM removal or occlusion, or incomplete AVM removal or occlusion.

### Outcomes

The primary outcome of the first RCT and of the registry is a composite of disabling stroke (resulting in modified Rankin Scale (mRS) > 2) or death from any cause at 10 years. Functional outcome status will be measured by the modified Rankin Scale, the most widely used outcome measure for stroke [43], using a standardized questionnaire administered by unblinded care personnel.

Secondary outcomes include overall mortality (all causes), overall morbidity (mRS > 2; all causes) at 1, 5 and 10 years, the occurrence of any neurological event during follow-up, the incidence of permanent (more than 3 months) disabling (mRS > 2) peri-operative (within 31 days) complications, the incidence of any peri-operative (within 31 days) complication, the incidence and number of hospital admissions, peri-treatment hospitalization lasting more than 15 days, discharge to a location other than home, occurrence of an ICH after enrollment and for up to 10 years, and occurrence of failure to eradicate the AVM (as determined by angiography) using the intended treatment modality.

The primary outcome of the nested RCT on pre-surgical or pre-radiation embolization is complete obliteration of the AVM (judged by local angiographers) combined with an independent functional outcome (mRS < 3; using a standardized questionnaire administered by unblinded care personnel) at the end of the management plan (no less than 3 months after the last procedure; no more than 3 years after radiation therapy).

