### Number of patients

The number of patients to be recruited depends on the specific trial hypotheses:i)Randomized comparison of interventional treatment and conservative management:

Interventional management of unruptured brain AVMs suitable to both conservative and curative treatment alternatives will lead to a decrease in the number of poor outcomes (defined as mRS >2) from 25 to 15 % at 10 years.i)Nested trial on the role of embolization in the treatment of brain AVMs:

Pre-surgical or pre-radiosurgery embolization of cerebral AVMs can decrease the number of treatment failures (failure to achieve: (angiographic cure with good outcome)) from 20 % to 10 %.ii)Secondary hypotheses:Curative treatment of cerebral AVMs can be accomplished with an acceptable up-front risk, defined as the occurrence of a treatment-related permanent disabling neurological complication in 10 to 20 % of patients or less (depending on AVM grade).Embolization of cerebral AVMs treatable by surgery or radiosurgery alone can be accomplished with an acceptable risk, defined as permanent disabling neurological complications of 8 % (3.4 to 12.6 %, 95 % CI).

Approximately 540 randomized patients (270 per group) are necessary to detect a hypothesized reduction of 10 % (from 25 to 15 %) in poor outcomes at 10 years, between interventional and conservative groups (all modalities included). It is too early to estimate the number of cross-overs that will occur; with a long follow-up period, losses can be substantial; analyses using the intention-to-treat principle would require a larger number, according to the proportion of cross-overs and losses to follow-up.

In theory, each management strategy should be separately validated, which would mean that for each modality, we would eventually need to recruit 540 patients or more.

For the nested study on pre-therapeutic embolization, 440 patients (220 per group) will be required to detect the hypothesized 10 % increase (from 80 to 90 %) in rate of success, defined as complete AVM eradication without the occurrence of a disabling complication.

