### Statistics

There are many components to this study (Table 2). It is important to distinguish the two randomized levels, which will be analyzed separately as randomized trials (intention-to-treat and per-protocol), and the registry portion, analyzed as an observational study.

**Table 2 Tab2:** Predefined group and subgroup analyses according to treatment allocation

Stratified randomized allocation	Groups: Intervention group versus Observation group
	Surgery subgroup versus Observation subgroup
	Radiosurgery subgroup versus Observation subgroup
	Embolization subgroup versus Observation subgroup
Randomization on pre-embolization	Groups: Embolization versus No embolization
	Embo + surgery subgroup versus Surgery alone subgroup
	Embo + radiosurgery subgroup versus Radiosurgery subgroup
Registry	
	Conservative management
	Surgical treatment (alone)
	Surgical treatment (with embolization)
	Radiotherapy (alone)
	Radiotherapy (with embolization)
	Embolization (alone)
	Embolization + surgery
	Embolization + radiotherapy
According to presentation	Unruptured AVM patients
	Ruptured AVM patients
According to SM grading	Low-grade AVM patients
	High-grade AVM patients

*AVM* arteriovenous malformation, *SM* Spetzler-Martin

Descriptive tables on demographic variables and potential risk factors will be provided to describe the groups at baseline. Continuous variables will be summarized in tables and will include the number of subjects, means, standard deviations, medians, minima and maxima. Categorical variables will be presented in tables as frequencies and percentages.

For the first RCT (interventional or conservative management strategy), the primary analysis, concerning the primary outcome (mRS > 2 or death from any cause at 10 years) of unruptured AVM patients will be analyzed using a Fisher’s exact test and the odds ratio with 95 % confidence interval will be reported. The same analysis will be performed for the ruptured group (considered a secondary analysis). All other secondary objectives and analyses for this first RCT will be analyzed in the same way.

The primary outcome of the second RCT (complete obliteration of the AVM combined with a mRS < 3; pre-surgical or pre-radiation embolization versus no embolization) will be analyzed with a logistic regression adjusted for ruptured status and intervention. Adjusted odds ratio and 95 % confidence interval will be reported. Moreover, stratified results by ruptured status and intervention will be presented.

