The patients entered in the registry will be included in secondary analyses designed to estimate treatment morbidity for each modality and natural history of untreated patients, just as an observational study, for unruptured and ruptured AVMs, for high-grade and low-grade lesions. There are four groups and eight registered subgroups (Table II). Predetermined subgroups that will be examined include: 1) according to treatment modality; 2) according to presentation (hemorrhagic versus all other presentations) and 3) according to SM AVM grade (I–II versus III–V). With a 10-year follow-up, it is likely that there will be losses to follow-up, but it is too early to estimate how many. Primary analyses will include three categories (good outcome; bad outcome; lost to follow-up). We will explore results when a best case scenario (patients lost to follow-up have a good outcome) and a worst case scenario (they have a bad outcome) are imputed.

All analyses will be done with SAS software (SAS Institute Inc., Cary, NC, USA) using a significance level of 5 %.

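### The nested trial's success is defined in two non-equivalent ways in the sample-size section, so it is unclear which endpoint the 80% and 90% rates describe for patients already dependent at entry

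*Protocol article*

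**What the plan says.** All places are in the Protocol article.

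- **Endpoint (Methods, Outcomes).** Nested-trial success is complete obliteration, judged locally, "combined with an independent functional outcome (mRS < 3; using a standardized questionnaire administered by unblinded care personnel"), at the end of the management plan. The Abstract and Statistics use the same mRS < 3 criterion, and Objectives speaks of an independent functional outcome. None of them refers to mRS at entry.
- **Hypothesis (Number of patients).** Embolization is to reduce "treatment failures (failure to achieve: (angiographic cure with good outcome)) from 20 % to 10" per cent.
- **Sample size (same section).** "440 patients (220 per group) will be required to detect the hypothesized 10 % increase (from 80 to 90 %) in rate of success", with success "defined as complete AVM eradication without the occurrence of a disabling complication".
- **Population.** Objectives admits ruptured and unruptured AVMs to the nested trial. Eligibility criteria says "Any patient with a brain AVM can be included in the randomized trial or registry portion of the study". No limit on entry mRS is given.
- **Analysis (Statistics).** The nested primary outcome "will be analyzed with a logistic regression adjusted for ruptured status and intervention". Entry mRS is not named. Table 1 lists a clinical assessment and a neurological examination at pre-entry but does not say whether mRS is scored there.

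**The concern.** Cure with a good outcome is a state at the end of the plan. Cure without a disabling complication is the absence of a new event. The two agree for a patient who enters independent and whose disability, if any, comes from treatment. They part for a patient who enters at mRS 3–5 after a haemorrhage, has the AVM eradicated without incident and remains at mRS > 2. That patient is a success in the sentence that sets the sample size and a failure in the endpoint that is analysed.

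In a sample that contains such patients, the same 80% and 90% cannot be the rates for both definitions. Patients who stay dependent whatever is done count as failures in both arms. They shrink the absolute difference and move both rates towards 50%, where the variance is larger. Whether 440 patients are enough depends on which definition the rates came from, and the article points both ways.

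**Working it through.** **Inputs.** From Number of patients: 80% v 90% success, 220 per group. From Statistics: "using a significance level of 5" per cent, with sidedness not stated. Power is not stated either. Two-sided 5% and 80% power are assumed because, with a continuity correction, they fit both sample sizes in the article. One-sided 5% with 90% power and no correction also fits approximately (217 and 273 per group against the stated 220 and 270), so the assumption is not unique.

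**Step 1: the stated figure.** With d = p2 − p1 and p̄ the mean of the two rates,

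n = [1.96·√(2p̄(1−p̄)) + 0.842·√(p1(1−p1) + p2(1−p2))]² / d²

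For 0.80 v 0.90: [1.96·√0.255 + 0.842·√0.25]² / 0.01 = 199 per group. The continuity correction (n/4)·[1 + √(1 + 4/(n·d))]² gives 219, or 438 in total against the stated 440. The same settings give exactly 270 per group for 25% v 15% in the first trial.

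**Step 2: the share dependent at entry.** The article gives no figure for the nested trial. Background reports a haemorrhagic presentation in 40–50% of patients and, of haemorrhage, that "perhaps only 10–20 % of survivors have long-term disability". Multiplying, 0.4 × 0.1 = 4% and 0.5 × 0.2 = 10%. This is an assumption: the figures are not for the nested population, and the disability they describe is not defined as mRS > 2.

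**Step 3: power if 80% and 90% are complication-definition rates.** Let a share f stay at mRS > 2 in both arms, with the rates holding in everyone else. The analysed rates become 0.80(1−f) and 0.90(1−f), and the difference 0.10(1−f).

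| f | Analysed rates | Power at 220 per group, uncorrected / continuity-corrected | n per group for 80% power, corrected |
|---|---|---|---|
| 0 | 80.0% v 90.0% | 84% / 80% | 219 |
| 4% | 76.8% v 86.4% | 74% / 70% | 275 |
| 5% | 76.0% v 85.5% | 72% / 67% | 290 |
| 10% | 72.0% v 81.0% | 61% / 56% | 370 |
| 20% | 64.0% v 72.0% | 44% / 40% | 558 |

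**Step 4: does the planned adjustment recover the loss?** A simulation of the logistic model with treatment and ruptured status (2,000 runs, half the patients ruptured, dependent patients only among the ruptured) gave power of 84%, 72%, 62% and 48% at f = 0, 5, 10 and 20%. Ruptured status recovers little, because most ruptured patients are not dependent.

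**Step 5: does entry mRS recover it?** In a similar simulation with 10% dependent at entry, adding entry mRS raised power from about 60% to 79% when none recovered, and from about 73% to 76% when half recovered.

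**Step 6: the other reading.** If 80% and 90% are already rates of cure with mRS < 3 in the population enrolled, f is contained in them. The planned size stays at about 219 per group and there is no loss.

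**The case against.** The strongest reply is that the hypothesis line names cure with good outcome, and that the 440-patient sentence refers back to that hypothesized difference. On this view the complication wording is a loose paraphrase, and the rates always belonged to the analysed endpoint. That is a fair reading and it removes the power loss. It does not remove the inconsistency: the sentence that fixes the sample size still states a different success, and nothing says that the rates allow for patients dependent at entry.

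A reader might go further and infer that the sample size counts only new disabling complications, or that the trial is shown to be underpowered. The article supports neither. The hypothesis line contradicts the first, and incomplete eradication is a failure under both definitions. The second needs the narrower reading, an assumed share dependent at entry, and no recovery to mRS < 3, although assessment may fall as late as 3 years after radiation therapy.

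It can also be said that the absolute threshold is deliberate. The Discussion defends a hard endpoint of death and dependency and extends that reasoning to the nested trial. This stands. Randomization keeps the comparison unbiased, and results will also be shown by ruptured status. A rule based on no worsening from entry would count a patient who stays at mRS 4 or 5 as a success, so it is a trade-off and not a correction.

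Lastly, a condensed article may leave baseline scoring and covariates to the full protocol. The absence of entry mRS is therefore not itself an error here. Because the article does name the covariates of this model, adding one is a reasonable proposal.

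**Conclusion.** The point holds as an inconsistency with a conditional consequence. The sample-size section gives two definitions of nested-trial success that differ for patients dependent at entry, such patients are not excluded, and the article does not say which definition carries the 80% and 90%.

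Under the complication reading, with 4–10% staying dependent, power at 220 per group is about 56–74% instead of 80–84%, and 275–370 per group would be needed for 80% power. Under the good-outcome reading the loss is zero. The range rests on two-sided 5%, background figures carried over to the nested population, and no recovery within the assumed share. What is at stake is dilution, power and the meaning of the planning rates, not bias.

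The argument does not carry over to the first trial. Its primary analysis is in unruptured patients and uses Fisher's exact test, which takes no covariate.

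**What to change.** 1. In Number of patients, restate the 440-patient sentence with the endpoint from Outcomes: complete obliteration plus mRS < 3.
2. State there that 80% and 90% are rates for that endpoint in the population enrolled, including patients dependent at entry. If they are not, restate the power or the sample size.
3. Score mRS at the existing pre-entry assessment with the same questionnaire, if this is not already done. Add entry mRS (0–2 v 3–5) to the nested logistic model alongside ruptured status and intervention.
4. Keep absolute mRS < 3 as the primary criterion. Eradication with no worsening from entry mRS may be added as a sensitivity analysis.

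The cost is a wording change, at most one extra score at an existing visit, and an adjusted odds ratio that is conditional on entry mRS. If almost no patient dependent at entry recovers, that stratum holds few or no successes, so the treatment estimate will rest mainly on patients independent at entry. The report should say so.
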